### Data management

All clinical results and MRI imaging data will be pseudonymized and stored in electronic case report form (eCRF) in an electronic database hosted by Research Electronic Data Capture (REDCap), a secure web application developed by Vanderbilt University, for building and managing academic databases (73) on a secure server at Charité—Universitätsmedizin Berlin, Germany. Regular monitoring in the form of independent data quality checks is ensured. OCT image data will be analyzed at Charité—Universitätsmedizin Berlin, Germany.

### Sample size considerations

The study is exploratory, and therefore, a formal sample-size computation is not possible. Hence, we justify the sample size by feasibility, which is *n* = 100 for MS-ON and *n* = 50 for AQP4-IgG+ON and MOG-IgG+ON. For each disease (MS-ON, AQP4-IgG+ON, and MOG-IgG+ON), patients will be stratified into subgroups according to the number of days since the onset of visual loss: 0–3 days, 4–7 days, and 8–30 days until high-dose corticosteroid treatment. With *n* = 50, the width of the 95% confidence interval for the treatment effects (=difference between visual acuities between these strata) is ~0.55 standard deviations of the mean difference depending on the actual number of patients within each subgroup.

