## Methods and analysis

### Study objectives

The primary objective of ACON is to investigate whether MS-ON, AQP4-IgG+ON, and MOG-IgG+ON patients treated with early high-dose corticosteroids for visual loss have better visual outcomes than those with late treatment. Treatment with both IVMP and oral high-dose corticosteroids is currently used as the standard of care in ON and will be included. According to previous data (24), subjects will be stratified into three groups: those presenting within 3 days of the onset of visual loss, those presenting between 4 and 7 days from the onset of visual loss, and those presenting between 8 and 30 days from onset of visual loss (days-to-Rx). The stratification will be performed within each respective disease group (MS, AQP4-IgG+NMOSD, and MOGAD).

Secondary objectives will consist of the interaction between clinical and para-clinical parameters, as well as their association with patient-reported QoL aspects (see Table 1; Figure 2).

**Table 1 T1:** Secondary objectives.

• Visual and structural outcomes of acute ON in patients treated with high-dose corticosteroid-therapy vs. plasmapheresis as first-line treatment.
• Visual and structural outcomes of MS-ON in patients treated with high-dose corticosteroid-therapy with oral prednisone taper vs. without taper as standard of care.
• Diagnostic and prognostic value of biomarker levels (NfL, GFAP) and associations with visual pathway damage (MRI- and OCT-based) in the acute stage and during follow-up.
• Characterization of MOG-IgG and AQP4-IgG levels and compartmentalisation (serum vs. CSF, using simultaneous paired samples) and associated risks for subsequent relapses in subjects with AQP4-IgG+ON and MOG-IgG+ON.
• Diagnostic value of OCT markers (e.g., increased pRNFL) for diagnosis of MS, NMOSD, and MOGAD.
• Prognostic value of OCT markers (e.g., increased pRNFL) for the visual outcome at 12-months follow-up.
• Diagnostic value of OCT markers for a conversion from acute ON to clinically definite MS.
• Diagnostic value of early clinical variables (i.e., visual loss and pain patterns).
• Investigation of the link between clinical symptoms (i.e., degree of visual loss and pain patterns) and lesion extension (detected using MRI and OCT).
• Characterization of visual function in daily routine, visual QoL scores and incidence of depression at 12-months follow-up.
• Interrelation of HC-BCVA and LC-BCVA and patient reported outcome measures at 6- and 12-months follow-up.

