#### Primary objective

We will estimate the treatment effect from a mixed model with visual acuity as an outcome variable, and the following fixed and random factors will be adjusted to the baseline:

Diagnosis (fixed; 3 levels)Days from visual loss (fixed; 3 levels: 0–3 days, 4–7 days, and 8–30 days until high-dose corticosteroid treatment)Dosage (fixed)Interaction between diagnosis and days since the visual loss (fixed)Eye (random; cluster effect to account for dependencies)Initiation of disease-modifying treatment (fixed; 2 levels)Center (random).

In case of interactions, diagnose-specific effects will be estimated from mixed models along with 95% confidence intervals.

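### The stated 95% CI width of about 0.55 SD with 50 patients does not follow from a comparison between three strata; read literally, it is about 1.36 SD

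*Protocol article*

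**What the plan says.** Under Sample size considerations, the protocol article calls the study exploratory and bases its numbers on feasibility: 100 patients for MS-ON and "50 for AQP4-IgG+ON and MOG-IgG+ON". Each disease is then divided by time to treatment into "0–3 days, 4–7 days, and 8–30 days until high-dose corticosteroid treatment". Study objectives confirms that the 50 patients are shared among the three strata: "The stratification will be performed within each respective disease group".

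The precision statement follows. It concerns "the width of the 95% confidence interval for the treatment effects", explained in the text as the "difference between visual acuities between these strata", and says that with 50 patients this width "is ~0.55 standard deviations of the mean difference depending on the actual number of patients within each subgroup". The article gives no stratum sizes, formula or SD, and no other precision or power figure.

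The Primary objective section of the statistical analysis uses the same three time levels in a baseline-adjusted mixed model. Diagnosis-specific effects with 95% confidence intervals are to be estimated if there are interactions. Nothing in that section needs correcting on this point; it shows that intervals of this kind are ones the study may report.

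**The concern.** A comparison between two of three strata uses only part of the 50 patients, so its interval must be clearly wider than one based on all 50. A full width of 0.55 SD, or about 0.28 SD either side, looks too narrow for groups of about 17.

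What is at stake is how the results will be read. The sentence tells readers what 50 patients can show about time to treatment in AQP4-IgG+ON and MOG-IgG+ON, the two smaller disease groups. If the true interval is much wider, a disease-specific estimate close to zero could be taken as evidence against an effect of timing when it is only imprecise.

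**Working it through.** **Inputs.** From Sample size considerations: 50 patients in a disease group, three strata, 95% confidence (z = 1.96). Assumed, because the article gives no split: equal strata, 50/3 = 16.7 each. Also assumed: SD is the between-patient SD of visual acuity, with no covariate adjustment.

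**Formula.** For strata of n1 and n2 patients, half-width = 1.96 × SD × sqrt(1/n1 + 1/n2). The full width is twice that.

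**Where 0.55 can come from.**
- Full width for one mean of all 50 patients: 2 × 1.96/sqrt(50) = 0.554.
- Half-width for two groups of 25: 1.96 × sqrt(2/25) = 0.554.

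The first is not a difference between strata. The second leaves the third stratum empty. The document does not show which calculation, if either, was used.

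**The described design, equal strata.** sqrt(2/16.7) = 0.346. Half-width = 1.96 × 0.346 = 0.68 SD; full width = 1.36 SD (1.39 with a t quantile on 47 df).

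| Reading of the stated 0.55 | Equal strata give | Ratio to 0.55 |
|---|---|---|
| Full width, between-patient SD | 1.36 | about 2.5 |
| Half-width, between-patient SD | 0.68 | about 1.2 |
| Full width, SD of a difference (sqrt(2) × SD) | 1.36/1.414 = 0.96 | about 1.7 |
| Half-width, SD of a difference | 0.68/1.414 = 0.48 | about 0.9 |

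If the unit meant the standard error of the difference, the full width would be 3.92 whatever the sample size.

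**Unequal strata (full width, between-patient SD).**
- 10/15/25: 10 v 15 gives 3.92 × sqrt(1/10 + 1/15) = 1.60; 10 v 25 gives 1.47; 15 v 25 gives 1.28.
- 8/12/30: 8 v 12 gives 1.79; 8 v 30 gives 1.56; 12 v 30 gives 1.34.

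Contrasts involving the smaller strata widen, while a contrast between larger strata can fall a little below 1.36.

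**Lower limit.** If n1 + n2 is at most 50, then 1/n1 + 1/n2 is at least 4/50. The full width is therefore at least 3.92 × sqrt(4/50) = 1.11 SD, reached only at 25 v 25 with nobody in the third stratum.

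**Size needed.** A full width of 0.55 SD needs 2 × (3.92/0.55)² = 101.6, about 102 patients per stratum.

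**MS-ON, 100 patients.** With 33.3 per stratum, sqrt(2/33.3) = 0.245; half-width 0.48 SD, full width 0.96 SD.

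**Baseline adjustment.** With correlation r between baseline and outcome, the width shrinks by sqrt(1 − r²). Going from 1.36 to 0.55 needs r = sqrt(1 − (0.55/1.36)²) = 0.91. The document gives no correlation.

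**The case against.** The strongest defence has four parts.

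*The unit and the word for width are loose.* The article speaks of standard deviations of the mean difference, not of visual acuity. If the unit is the SD of a difference and the figure is a half-width, a 12/13/25 split gives 1.96 × sqrt((1/12 + 1/13)/2) = 0.555 for the 12 v 13 contrast. A reader might infer that no interpretation reaches 0.55 with three occupied strata. That is too strong, as this example shows. It does, however, need two departures from the plain reading and a particular split, none of which the article states.

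*The sentence is hedged.* It adds "depending on the actual number of patients within each subgroup". On the literal reading this does not help, because no split of 50 goes below 1.11 SD.

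*The planned analysis is not an unadjusted comparison.* This stands in part. The primary model is baseline-adjusted and covers all three diagnoses, with further fixed and random terms. Adjustment may narrow the interval, and the other terms may change it. So 1.36 and 0.96 are unadjusted approximations, not the widths that the model will deliver.

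*The study is exploratory and sized by feasibility.* This stands. A reader might infer that the sample size depends on the 0.55 figure and falls with it. The article says otherwise: the numbers come from feasibility, and no power claim or decision rule uses the figure.

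A reader might also infer from the 0.68 SD half-width that true effects below about 0.7 SD cannot be detected. The half-width says which *observed* differences would exclude zero. With equal strata, a true difference of 0.5 SD would still do so about 30% of the time (0.5/0.346 = 1.44; normal probability above 1.96 − 1.44 = 0.52), and one of 0.68 SD about half the time.

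The point is not a matter of detail left to a fuller document: the article states this figure, and its own patient number and strata contradict it.

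**Conclusion.** The point holds: the precision figure is wrong as written. The factor of 2.5 rests on equal strata, a full width, the between-patient SD and no adjustment. It should not be quoted without those conditions, since the other single-change readings give factors of about 1.2 and 1.7. The bound of 1.11 SD does not depend on how the patients are split, but it does assume the literal reading of width and unit and no adjustment.

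This is a correction to a descriptive statement. It gives no reason to change the sample size, the strata or the model. It matters because nothing else in the document tells readers how precise the disease-specific comparisons will be.

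**What to change.** Replace the sentence under Sample size considerations with:

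> With n = 50 and three equal strata (about 17 each, assumed), the unadjusted 95% CI for a pairwise difference is about ±0.68 SD (full width 1.36 SD), where SD is the between-patient SD of visual acuity; with n = 100 it is about ±0.48 SD (full width 0.96 SD). With unequal strata, contrasts involving the smaller strata are wider (for example, full width 1.28 to 1.60 SD across the contrasts of a 10/15/25 split of 50). Baseline adjustment may narrow these intervals.

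If the authors meant a half-width or another SD unit, they should say so and give the stratum sizes behind the figure.

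The cost is a short rewording with no extra patients and no change to the analysis. The downside is that the stated precision becomes less favourable.

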### Statistical analysis

For data analysis, subjects will be assigned into groups according to their diagnosis at the 6-month follow-up. For the primary objective, data from subjects with a diagnosis of MS, AQP4-IgG+ NMOSD, and MOGAD will be analyzed. Data from subjects with other diagnoses (other autoimmune, e.g., CIS-ON, seronegative non-MS-ON) will be described and characterized separately but not included in the primary analysis.

#### Primary objective

We will estimate the treatment effect from a mixed model with visual acuity as an outcome variable, and the following fixed and random factors will be adjusted to the baseline:

Diagnosis (fixed; 3 levels)Days from visual loss (fixed; 3 levels: 0–3 days, 4–7 days, and 8–30 days until high-dose corticosteroid treatment)Dosage (fixed)Interaction between diagnosis and days since the visual loss (fixed)Eye (random; cluster effect to account for dependencies)Initiation of disease-modifying treatment (fixed; 2 levels)Center (random).

In case of interactions, diagnose-specific effects will be estimated from mixed models along with 95% confidence intervals.

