#### Potential bias and methods to reduce bias

Since this study is observational and thus randomization and masking to treatment assignment are not possible, it has potential sources of the known bias. First, the study has a selection bias, as some people do not present in the clinic for an inaugural ON at all or are more likely to present with a more severe ON. To mitigate this, a patient's medical history is assessed in a semi-standardized way to detect potential previous attacks, leading to study exclusion. In addition, an ophthalmological examination is conducted to assess for evidence of prior ON damage. Furthermore, prior polling of participating centers carried out in 2021/2022 regarding the number of patients with acute ON seen in each clinic demonstrates the feasibility of including a representative population of subjects with inaugural ON of all severities.

Second, the study has a confounder bias, as subjects will receive treatment according to their time of presentation at the hospital as the standard of care. Furthermore, disease-modifying treatments and other medication initiated between the baseline and follow-up will be analyzed as potential confounders. While high-dose corticosteroid treatment cannot be delayed for ethical reasons, a thorough record will keep the process transparent, and confounders will be minimized by advanced biostatistical techniques, such as confounder adjustment.

Information bias may be introduced when recording the primary visual outcomes, stemming from differences in visual acuity recording techniques, room lighting, and different physicians measuring visual acuity. Therefore, a training course for all participating centers will be held, which aims to standardize assessments across centers. To overcome analytic differences within different OCT machines, we have developed a pipeline for device-independent intraretinal layer OCT segmentation (74), allowing for standardized analysis regarding the region of interest and layer boundaries. Additional potential biases include OCT-captured artifacts for which ACON agreed to adhere to the APOSTEL guidelines for performing and reporting OCT measurements (75). Similarly, different MRI techniques pose another source of information bias. To counteract this, ACON will offer short MRI evaluation training to the participating centers, focusing on the interpretation of optic nerve abnormalities.

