Moreover, the ACON study will provide invaluable insights into the course of these diseases. Particularly, ACON has the capacity to give novel insights into MOGAD for which the proportion of monophasic vs. relapsing cases is far from clear (8). Given a follow-up of 12 months minimum (a longer observation period is envisioned), the study will also generate data on the implementation of preventative immunotherapy (when to treat, whom to treat, and potentially which drug to use?). While there is broad consensus that immediate immunotherapy after diagnosis is indicated in AQP4-IgG+NMOSD given the high risk of recurrence and poor prognosis if left untreated (93–95), the situation is less clear in MS and MOGAD (96, 97), and finally, in light of the rapidly changing treatment landscape with approved drugs for AQP4-IgG+NMOSD and several clinical trials in MOGAD currently underway, the ACON study will collect clinically useful data on individual treatment sequences for on-label or off-label immunotherapies in patients with acute ON (97–100).

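### The primary model adjusts the early-versus-late corticosteroid contrast for disease-modifying treatment started after the exposure, which puts that contrast at risk of bias

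*Protocol article*

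**What the plan says.** The protocol article, under Statistical analysis, Primary objective, sets a mixed model with visual acuity as outcome. The exposure is "Days from visual loss (fixed; 3 levels: 0–3 days, 4–7 days, and 8–30 days until high-dose corticosteroid treatment". The other terms are diagnosis ("Diagnosis (fixed; 3 levels"), dosage, the interaction of diagnosis with time stratum, random effects for eye and center, and "Initiation of disease-modifying treatment (fixed; 2 levels". The list is introduced by the statement that "the following fixed and random factors will be adjusted to the baseline". No baseline variable is named there.

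The section Potential bias and methods to reduce bias says that "disease-modifying treatments and other medication initiated between the baseline and follow-up will be analyzed as potential confounders". It also says that patients are treated according to when they present at the hospital, and it promises confounder adjustment in general terms.

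Age, sex and race are recorded (Medical history and clinical examination). High-contrast acuity is mandatory at baseline, 6 and 12 months (Table 3).

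**The concern.** A confounder of the timing effect must precede the delay, or at least not follow from it, and must influence both delay and visual outcome. Disease-modifying treatment begun between baseline and follow-up comes after presentation, and presentation is what sets the delay. It can therefore be a consequence of the exposure but not a cause of it.

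Two things can then go wrong. If late corticosteroids lead to poorer recovery or early relapse, and these prompt a disease-modifying drug, the term holds constant part of what the study wants to measure. If unmeasured severity also drives recovery and hence the decision to start the drug, conditioning on the drug links delay to severity even where they were unrelated.

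The primary objective is whether earlier treatment gives better vision, and the Discussion hopes to establish acute treatment standards. A term that may pull the main contrast towards zero therefore matters, even in a study described as exploratory.

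**Working it through.** **Order of events.** Delay runs from visual loss to corticosteroids, 0 to 30 days. The bias section ties it to presentation and puts disease-modifying treatment after baseline. The order is delay, then disease-modifying treatment, then acuity at follow-up. The label of potential confounder does not fit that order.

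**Is there a figure to reproduce?** No. The documents give no rate of initiation, no dependence of initiation on recovery, and no expected effect of delay. Every number below is an illustration on assumed inputs.

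**Illustration 1: initiation depends on recovery.** 400,000 simulated patients per run, with U an unmeasured severity and the e terms independent standard normal noise:

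- early recovery M = −0.5·late − 0.7·U + 0.7·e1
- initiation follows a probit model on −g·M, so poorer recovery makes it more likely when g > 0
- outcome Y = 0.8·M − 0.2·U + 0.4·e2

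The true total effect of late treatment is 0.8 × (−0.5) = −0.40. Multiplying by the ratio of the coefficient with the term to that without it gives:

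| g | ratio | estimate with the term | attenuation |
|---|---|---|---|
| 0 | 1.00 | −0.40 | none |
| 0.3 | 0.94 | −0.38 | 6% |
| 0.6 | 0.81 | −0.32 | 19% |
| 1.0 | 0.63 | −0.25 | 37% |

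If the drug is also given a true benefit of 0.2 on the outcome, the ratios for g = 0.3, 0.6 and 1.0 become 0.97, 0.85 and 0.67, so the attenuation is 3%, 15% and 33%.

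**Illustration 2: different assumptions.** 1,000,000 simulated patients, a direct late-versus-early effect of 0.20 logMAR, and no link between severity and delay. Initiation depends on delay and disease activity, and the drug has a small benefit (0.05 logMAR). The total effect is 0.190 and the model with the term returns 0.172, so the attenuation is (0.190 − 0.172)/0.190 = 9.5%. Without the term the model returns 0.190. When initiation is unrelated to delay and activity, the term does no harm (0.201 against 0.200).

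**AQP4-IgG+ON.** Extending the first illustration to three diseases with g = 0.6: if every AQP4 patient starts treatment, the AQP4 timing contrast is −0.398 with or without the term. At 96% uptake it is −0.412 without and −0.395 with, a change of 0.017/0.412 = 4%.

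**Why the baseline wording matters.** Suppose severe attacks are treated sooner (assumed log-odds of late treatment −0.5 or −1.0 per SD of severity) and severity is not adjusted for. With initiation unrelated to delay, a true 0.200 is then estimated as 0.130 or 0.075. With severity in the model and the treatment term out, it is recovered (0.201 and 0.198). This shows what hangs on the meaning of the baseline clause. It does not show that the plan leaves severity out.

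**The case against.** The strongest reply is that no passage says initiation depends on delay or recovery. The Discussion describes a consensus that "immediate immunotherapy after diagnosis is indicated in AQP4-IgG+NMOSD", which ties the decision to diagnosis, and diagnosis is already in the model. With no link there is no bias, as the g = 0 row shows. This stands: the bias is a risk and has not been demonstrated. But the same Discussion calls the position in MS and MOGAD less clear. The decision is discretionary there and could follow the course of the attack.

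A second reply is that the term may stand in for pre-treatment differences between patients. If so, adjusting for those differences directly is safer than adjusting for a later decision.

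Some stronger readings are tempting, and the documents do not support them:

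- *The contrast is distorted both by the treatment term and by omitted confounders.* Neither distortion is shown. The remark that people "are more likely to present with a more severe ON" stands under selection bias and concerns who presents, not how soon.
- *No pre-treatment patient factor is listed.* Diagnosis is listed and reflects the underlying disease, although "subjects will be assigned into groups according to their diagnosis at the 6-month follow-up". The baseline clause may well mean baseline acuity. Further covariates may be named in an analysis plan not shown here, so their absence from an article carries little weight.
- *A shared treatment term is imposed on AQP4.* A near-constant term is absorbed by the diagnosis effect and hardly moves the AQP4 contrast. The plan also foresees diagnosis-specific models in case of interaction.
- *Onset in one or both eyes is collected and ignored.* It is not named among the variables in the data-collection sections or Table 3.

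**Conclusion.** The concern holds for the treatment term. Including it is a stated modelling choice, made in the model and repeated in the bias section, so an unseen analysis plan does not explain it away. A variable that follows the exposure is in the primary model under the wrong label, and the primary contrast is at risk of bias. The size runs from none to 37% attenuation. That range rests on assumed links between recovery and initiation, and the documents settle neither size nor direction. The unclear baseline wording and the unnamed demographic covariates are worth settling in the same edit but do not carry the point.

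**What to change.** 1. Remove initiation of disease-modifying treatment from the primary model. Report it by time stratum and diagnosis, or in a sensitivity analysis labelled as conditioning on a variable that follows the exposure.
2. Reword the bias section so that drugs started after baseline are not called confounders of time to corticosteroids.
3. State that adjustment to the baseline means baseline high-contrast best-corrected acuity as a covariate. Report the contrast with and without it, because it is measured on different days of the disease across strata and may already reflect the delay.
4. Add age, sex and race to the primary model.

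All of this uses data already collected and should be settled before outcomes are analysed. The cost is a change of wording, the additional analyses and a few degrees of freedom. The primary estimate will also no longer separate out the effect of later disease-modifying treatment, and the report should say so.

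### Disease-specific effects of time to treatment, which the primary objective asks for, are estimated only if an undefined interaction condition is met, and that condition would be weak as a significance test

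*Protocol article*

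**What the plan says.** In Study objectives, the primary aim reads: "investigate whether MS-ON, AQP4-IgG+ON, and MOG-IgG+ON patients treated with early high-dose corticosteroids for visual loss have better visual outcomes than those with late treatment". The same section adds: "The stratification will be performed within each respective disease group (MS, AQP4-IgG+NMOSD, and MOGAD".

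Sample size considerations is also organised by disease. It plans 100 patients with MS-ON and 50 with each antibody-associated form, split by time to treatment within each disease. For n = 50, the size of one antibody group, the width of the 95% interval for the difference between time strata "is ~0.55 standard deviations of the mean difference depending on the actual number of patients within each subgroup". The section declares: "The study is exploratory, and therefore, a formal sample-size computation is not possible".

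The Primary objective part of Statistical analysis fits one mixed model for visual acuity. Its fixed terms include diagnosis, time to treatment ("3 levels: 0–3 days, 4–7 days, and 8–30 days until high-dose corticosteroid treatment") and "Interaction between diagnosis and days since the visual loss (fixed"). It then says: "In case of interactions, diagnose-specific effects will be estimated from mixed models along with 95% confidence intervals". It does not say what counts as an interaction, at what level it is judged, or what is reported when none is found.

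**The concern.** The objective and the sample size are framed by disease, but the estimates that answer them depend on a feature of the data. If the condition is not met, the text promises no early-versus-late estimate for any of the three diseases.

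Interaction tests need far more patients than main effects, and here 200 patients are spread over nine cells. Absence of a detected interaction would say little about whether the three diseases respond alike, but the rule invites that reading. The protocol itself gives reasons to expect differences: the Introduction says the three entities need different treatment strategies, and the section on hyperacute corticosteroids cites retrospective evidence of benefit in AQP4-IgG+ON and MOG-IgG+ON. A condition left undefined also lets the choice of primary estimate follow the results.

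**Working it through.** **The plan's own figure.** The article states no power, only the interval width of about 0.55 SD at n = 50. This is 2 × 1.96/√50 = 0.554 (full width for one mean of 50) or 1.96 × √(2/25) = 0.554 (half-width for 25 versus 25). With three equal strata of 50/3 ≈ 16.7, the half-width for two strata is 1.96 × √(2/16.7) = 0.68 SD and the full width 1.36 SD. For MS-ON (33.3 per stratum) the half-width is 1.96 × √(2/33.3) = 0.48 SD.

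**Inputs for the interaction test.**
- From the protocol: 100/50/50 patients; three diagnoses by three strata, so (3−1)(3−1) = 4 df for the interaction.
- Assumed, because not stated: residual SD 1; alpha 0.05 (0.10 and 0.20 also tried); early-late effect d = 0.5 SD (1.0 SD also tried); no effect in MS-ON.
- Stratum splits tried (0–3/4–7/8–30 days): equal thirds, 40/30/30, 25/35/40, 20/30/50%.
- Shapes tried: linear (0, d/2, d), step after day 3 (0, d, d), step after day 7 (0, 0, d).
- Groups affected: both antibody groups, one only, or (linear shape) one fully and the other by half.

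**Formula.** With the same split in each disease, the noncentrality is λ = N × d² × V_dx × V_time. V_dx is the weighted variance of the group multipliers (weights 0.5, 0.25, 0.25) and V_time that of the shape across strata. Power is the upper tail of the noncentral F with 4 and 200 − 9 = 191 df.

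**Results at d = 0.5, alpha 0.05.**

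| Scenario | V_dx | V_time | λ | Power |
|---|---|---|---|---|
| Both groups, linear, equal strata | 0.25 | 0.1667 | 2.083 | 17.4% |
| One group, linear, equal strata | 0.1875 | 0.1667 | 1.563 | 13.9% |
| Lowest tried: one full, one half, linear, 20/30/50 | 0.1719 | 0.1525 | 1.311 | 12.3% |
| Highest tried: both groups, step after day 7, 20/30/50 | 0.25 | 0.25 | 3.125 | 24.8% |

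The test would therefore miss the difference in about 75–88% of studies.

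**Sensitivity.** Unless noted: d = 0.5, linear shape, equal strata, one or both groups affected.
- Alpha 0.10: 23–27%. Alpha 0.20: 37–42%, and about 52% in the most favourable scenario of the table (λ = 3.125).
- Baseline adjustment divides λ by 1 − ρ². For ρ = 0.5, power is 17–22%. For ρ = 0.7, it is 24–32%, and about 47% in the most favourable scenario (3.125/0.51 = 6.13).
- Study population expects 300 screened and 30–50% ineligible, so 150–210 eligible. At N = 150 power is 11–14%; at N = 210 it is 14–18%.
- d = 1.0 quadruples λ. Over all splits and shapes it runs from 5.24 to 12.5, and power from 41% to 81%.

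**If a common effect were reported instead.** An additive fit weights the diseases by size. With 0.5 SD in both antibody groups it gives (100×0 + 50×0.5 + 50×0.5)/200 = 0.25 SD. With one group it gives (50×0.5)/200 = 0.125 SD. Equal weighting of the three diagnoses would give 0.33 and 0.17 SD. Each version understates the effect where it exists and ascribes one to MS-ON.

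**The case against.** The article never says that the condition is a significance test. It states no alpha, lists the interaction as a fixed term with no rule for dropping it, and names no pooled effect. Precision is already described for strata at the size of one antibody group, so disease-specific intervals were plainly in mind. The study is declared exploratory, and the definition of the condition may sit in an analysis plan that is not shown.

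Much of this stands. A reader might infer that the plan has 17% power to detect an interaction. That figure belongs to one scenario (0.5 SD in both antibody groups, linear, equal strata, alpha 0.05, no gain from baseline adjustment) and is not a property of the plan. A reader might also infer that a misleading pooled effect would usually be reported. The documents do not support that, because they name no fallback; the dilution figures hold only if a common effect is reported. Nor does prognosis single out MS-ON as the disease without benefit: the Introduction gives a good visual prognosis for MOG-IgG+ON as well.

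The conditional rule itself does not go away. It is written in the protocol and conflicts with the objective there, so it is more than detail left to another document. An exploratory study justified by interval width has all the more reason to report its intervals unconditionally.

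**Conclusion.** The point holds as a mismatch between objective and analysis: the protocol asks its primary question by disease and makes the answer conditional on an undefined finding. Its size depends on how the condition is read. As a 5% test of the 4-df interaction, it would miss a 0.5 SD difference in most studies under every split and shape tried. Relaxing alpha to 0.20 only brings detection to roughly even odds in the most favourable case. For differences near 1.0 SD the test does better. All of this rests on assumed effect sizes, alpha, splits and residual SD. Two conclusions do not: a non-detected interaction cannot be taken as evidence of a common effect, and the disease-specific estimates should not depend on detecting one.

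**What to change.** In the Primary objective part of Statistical analysis, delete the opening condition of the last sentence and write instead: *Early-versus-late contrasts with 95% confidence intervals are estimated for each diagnosis from the model with the diagnosis-by-days interaction and are always reported. The interaction test is reported as supportive information, and any effect pooled over diagnoses is secondary.*

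The cost is one sentence. The interaction is already in the model, so no further data or model is needed. The downside is that the disease-specific intervals will be wide. With equal strata, power to detect 0.5 SD within one disease is about 30% at n = 50 and 53% at n = 100. The change makes the analysis answer the stated question but does not cure that imprecision.
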